### Allocation concealment

A Random allocation sequence will be implemented using numbered sealed envelopes opened after inclusion of the patient for the study.

### Implementation

After inclusion of the patient the study the nurse will open the numbered envelope and prepare five 10 cm^3^ syringes with study drug or placebo according to randomization and pass them to the enrolling physician and nurse who will administer the drug.

### Blinding

The study will be conducted in double-blind fashion. The patient, enrolling physician, nurse who administering the drug, and clinician reviewing the clinical outcomes will all be blinded to the treatment. The statistician, study nurse who prepares the syringes and clinician involved in safety control will be unblinded to the patient’s assignment.

## Statistical methods

### Sample size

The clinical efficacy of antazoline was assumed using data derived from Srzednicki *et al.* 1990 [8], the most credible publication available. Assumption of 50% efficacy in AF conversion is conservative, since the authors reported efficacy over 70% in doses not exceeding 250 mg of antazoline. Assumption of 5% efficacy of placebo was derived from studies over vernakalant [3-6]. Using a two-tailed test, a type I error of 0.01, a power of 90% and a 20% drop-out rate to fulfill the criteria of intention-to-treat analysis, we calculated that we need 80 patients, 40 in each group, to show the superiority of antazoline over placebo.

### Data management

During the study, the investigator will regularly enter information into case report forms (CRFs). Database management and quality control for this study will be the responsibility of the Department of Biostatistics (this is an independent statistician). Structured data elements from the CRFs will be entered into the database and reviewed using double data entry for verification. Information entered into the database will be systematically checked and obvious errors will be corrected. Omissions or questions will be returned to the investigator for resolutions.

### Statistical analysis

All analyses will be conducted using SAS software (version 9.2., SAS Institute Inc., Cary, NC, USA. The Kolmgorov-Smirnov test will be used to check for normal distribution of continuous data. Normally distributed continuous data will be presented in terms of mean ± standard deviation. They will be compared across two groups with the two-sided unpaired t-test or Cochran-Cox test when there is heterogeneity of variance (evaluated by the F-Snedocor test). Non-normally distributed continuous data will be reported in terms of percentiles (for example, median and inter-quartile range) and will be compared across two groups by Wilcoxon rank-sum test. Student’s paired *t*- or Wilcoxon’s test will be used as appropriate to compare continuous variable differences between baseline and the end of the observation period. Categorical variables will be summarized in terms of frequencies and percentages. A comparison between them will be performed by Pearson’s χ^2^ test with continuity correction or Fisher’s exact test, if the expected cell count will be less than 5. The probability of return to SR (by the time from AF) by the treatment group will be graphically displayed according to the method of Kaplan–Meier, with comparison of cumulative events by the log-rank test. Multivariate analysis will be carried out using Cox proportional hazards regression modeling. All hypotheses will be two-tailed with a 0.05 type I error.

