### Participants

All patients with AF lasting less than 43 hours reporting to the emergency room (ER) or clinical ward of our center will be considered for inclusion.

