### Time window

The AnPAF Study is designed both for symptomatic and asymptomatic patients.

In symptomatic patients the self-reported onset of symptoms is considered when determining the time of AF episode. In symptomatic patients on long term antiarrhythmics or oral anticoagulants the self-reported onset of symptoms of a recent episode of AF is considered when determining the inclusion criteria.

In asymptomatic patients a medical documentation of SR within the last 43 hours must be available to enroll the patient (for example ECG strip).

In order to ensure patients’ safety in all ambiguous or controversial cases patients will not be considered for enrollment.

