#### Study group

Patients assigned to the antazoline group will be administered antazoline in boluses of 50 mg diluted to 10 cm^3^ every five minutes up to a cumulative dose of 250 mg or conversion of AF to SR. Drug administration will also be stopped in case of an adverse event (see Outcomes section) or conversion of AF to a different supraventricular arrhythmia. BP will be measured before every injection.

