### Outcomes

All clinical outcomes will be assessed by the enrolling physician and later adjudicated by an experienced cardiologist both blinded to patients assignment.

All safety outcomes will be assessed by the enrolling physician blinded to patient’s assignment. In order to provide maximum safety for the patient, a physician unblinded to patent’s assignment but not involved in the clinical outcomes assessment will be available at the study site at all times.

**Primary outcome:** conversion of AF to SR confirmed in standard 12-lead ECG during the observation period

**Secondary end points:** time to conversion; return of AF during observation period; serious adverse event defined as **every** adverse event requiring hospitalization or prolonged observation

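### The time-to-sinus-rhythm curves are planned on time from AF, not time from first bolus, so they would mainly show the wait before enrolment (should-fix, exploratory analysis)

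*Protocol article*

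**What the plan says.** In the protocol article, under Statistical analysis: "The probability of return to SR (by the time from AF) by the treatment group will be graphically displayed" by the Kaplan-Meier method, "with comparison of cumulative events by the log-rank test". The next sentence is "Multivariate analysis will be carried out using Cox proportional hazards regression modeling"; it names neither a time origin nor covariates.

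Under Outcomes, the secondary endpoints include "time to conversion; return of AF during observation period", again without a starting point. No section starts the clock at randomisation or first bolus.

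Three other sections fix what a clock based on AF would contain:

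- Participants: "All patients with AF lasting less than 43 hours reporting to the emergency room (ER) or clinical ward" are considered for inclusion.
- Time window: "In symptomatic patients the self-reported onset of symptoms is considered when determining the time of AF episode". For the others, "In asymptomatic patients a medical documentation of SR within the last 43 hours must be available to enroll the patient".
- Study group: antazoline is given "in boluses of 50 mg diluted to 10 cm^3^ every five minutes up to a cumulative dose of 250 mg". Under Interventions, observation then runs 1.5 hours past the last dose.

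The stated aim, at the end of the Background, is to assess rapid conversion.

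**The concern.** Every patient must still be in AF at enrolment, so the hours before enrolment cannot contain a study conversion. A Kaplan-Meier estimate on time from AF that ignores delayed entry counts those hours as time at risk. This has three consequences:

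- The position of the curve is set by how long patients had been in AF before they arrived, not by how fast the drug acts.
- The height of the curve stops estimating the conversion proportion. Patients leave the risk set in order of their wait, and a conversion in someone with a long wait is divided by a very small number at risk.
- In asymptomatic patients onset is only bounded by the last documented sinus rhythm, so their time zero is not known.

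At stake is a published figure for time to conversion that would show far more conversion than occurred, over tens of hours, for a drug expected to act within minutes.

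**Working it through.** **Inputs from the article.** AF duration at entry below 43 h. At most 250/50 = 5 boluses, 5 minutes apart, so the last is at 4 × 5 = 20 min. Observation lasts 90 min after the last dose. Conversion is 50% versus 5%, with 40 per arm. Alpha is 0.01 in the sample size section and 0.05 in the analysis section; both are used below, and the mismatch is a separate matter.

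**Assumptions, not in the article.** AF duration at first bolus is either uniform over 1–43 h or exponential with mean 10 h capped at 43 h. Conversions fall 2–25 min after first bolus. Non-converters are censored at 110 min.

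**The plan's own figure.** The article gives no figure for this analysis; its N is for the binary endpoint. With mean proportion 0.275 and difference 0.45:

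- n = [2.576·√(2·0.275·0.725) + 1.282·√(0.05·0.95 + 0.5·0.5)]² / 0.45² = 26.7
- With continuity correction: (26.7/4)·[1 + √(1 + 4/(26.7·0.45))]² ≈ 31 per arm
- With 20% drop-out: 31/0.8 = 38.75, so 39 per arm and 78 in total, close to the stated 80

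Nothing in this depends on the clock.

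**Share of the axis under treatment.** 20 + 90 = 110 min = 1.83 h. The longest possible axis is 43 + 1.83 ≈ 44.8 h, and 1.83/44.8 ≈ 4%.

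**Median, closed form.** Let F be the distribution of AF duration at entry and p the conversion proportion. Ignoring the short follow-up, the naive curve is S(t) = (1 − F(t))^p.

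- Uniform, p = 0.5: S = 0.5 needs F = 0.75, so t = 1 + 0.75·42 = 32.5 h. Simulation: about 33 h.
- Exponential, p = 0.5: exp(−t/20) = 0.5, so t = 20·ln 2 = 13.9 h. Simulation: about 15–16 h, later because non-converters stay at risk longer than converters.

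The median moves with the assumed wait.

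**Height of the curve.** If all 40 patients in an arm left the risk set strictly in order of wait, the expected final value would be 1 − ∏(1 − p/k) over k = 1 to 40. That is 0.91 for p = 0.5 and 0.19 for p = 0.05. Simulation with the real follow-up times gives:

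| True conversion | First-bolus clock | AF clock |
|---|---|---|
| 50% | 50% | about 85% (uniform) to 89% (exponential) |
| 5% | 5% | about 15–16% |

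**Speed.** Suppose 55% convert at exactly 10 min, or 55% at exactly 80 min (uniform wait over 0.5–43 h). From first bolus the medians are 0.17 h and 1.33 h, a ratio of 8. From AF onset they are 31.5 h and 32.3 h, a ratio of about 1.03.

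**Log-rank test, 40 per arm.**

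| True rates | Alpha | First bolus | AF clock |
|---|---|---|---|
| 50% v 5% | 0.01 | about 0.99 | about 0.95 |
| 50% v 5% | 0.05 | about 1.00 | about 0.99 |
| 30% v 5% | 0.01 | about 0.70 | about 0.59 |
| 30% v 5% | 0.05 | about 0.88 | about 0.81 |

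With 30% in both arms, rejection on the AF clock at nominal 0.05 was about 0.05–0.06.

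**Would delayed entry rescue the AF clock?** Not at this size. With uniform waits about 3.6 of 80 patients are at risk per event, and null rejection at nominal 0.05 was 0.069–0.075.

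**The case against.** **The wording may be loose.** The phrase does not contain the word onset, and it could be shorthand for the time a patient takes to go from AF to sinus rhythm. A condensed article may also leave the exact clock to an analysis plan. This deserves weight, but the article does not stay silent: it names an origin, and no other section supplies a treatment-based one. A programmer following the sentence would draw the wrong curve, so it needs correcting even if nobody meant it literally.

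**Stronger readings that the documents do not support.**

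- A reader might infer from the immortal time that the comparison between arms is biased or the log-rank test invalid. It is not. Randomisation makes the wait comparable between arms and the type I error holds; the costs are some power and the information on speed.
- A reader might infer that the trial can no longer answer its question. The primary outcome is conversion within the observation period. It is binary and does not use this clock.
- A reader might take the Cox model to run on the AF clock. That sentence states no origin, so this cannot be asserted.
- A reader might quote the 33-hour median as a prediction. It rests on a uniform AF duration that the article does not give, and an exponential one halves it.

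**The endpoint is exploratory.** The Abstract and Objectives declare this for presumed lack of power. That stands and limits the severity. It excuses imprecision, but not a curve that displays 85% when the truth is 50%.

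**Conclusion.** The point holds as a should-fix. Taken as written, the Kaplan-Meier display would mainly describe AF duration before enrolment and would overstate conversion in both arms. The overstatement depends on the two assumed AF-duration distributions, but its direction and rough size were the same under both. The loss of log-rank power is small at the planned effect and moderate (about 7 to 11 percentage points) at 30% versus 5%. The conclusion rests on the plain reading of the phrase and on an analysis without delayed entry, which the article does not mention.

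**What to change.** Replace the parenthesis in the Kaplan-Meier sentence with time from first bolus (or from randomisation, which also gives a start time to anyone randomised but not dosed). Use this origin for the curves and the log-rank test, and state the same origin for the Cox model. Censor non-converters at the end of their own observation period, so that the curve agrees with the primary endpoint.

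Optional: enter AF duration at baseline as a Cox covariate, with a stated rule for asymptomatic patients, whose onset is only bounded. A common cut at 90 min is also possible but not needed; it would drop any conversions between 90 and 110 min from the curve.

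The cost is a few words and a programming change. The sample size, the primary analysis and patient management do not change. The article reports that the trial is recruiting, so the case report form can still be checked for exact bolus and conversion times, which the existing endpoint needs in any case.

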## Background

Atrial fibrillation (AF) is considered to be not only a medical but also a social problem. It is related to the elevated risk of thrombo-embolic events with a stroke being the most important and it adversely affects life expectancy and quality. The cornerstone of AF therapy is a long-term antithrombotic treatment followed by adequate rhythm or rate control [1,2]. The pharmacological cardioversion (CV) of AF to sinus rhythm (SR) may be achieved by administration of class IA, IC and III antiarrhythmic drugs: flecainide, ibutilide, dofetilide, propafenone or amiodarone [1,2]. Beta-adrenergic blocking agents are not considered suitable for pharmacological CV due to their low or lack of efficacy. Another drug recently introduced for rapid CV of AF is vernakalant [3-6]. Pharmacological CV may be related to potential pro arrhythmia, lack of efficacy or exceptionally high cost of a compound used.

So far there is no significant evidence of superiority of either rate or rhythm control strategies in terms of mortality, severe AF complication rates, worsening of heart failure quality of life of patients with AF. A hypothesis that deleterious effects of antiarrhythmic drugs may have offset the benefits of SR in those patients is seriously considered. Therefore a decision of SR restoration and maintenance for a long time should be patient-tailored and based on the individual patient’s history, symptoms and preferences [1].

Antazoline is a first generation antihistaminic agent with chinidine-like and anticholinergic properties. Antazoline prolongs action potential duration and lowers its amplitude, prolongs phase 0 duration, reduces phase 4 of resting potential and reduces excitability of cardiac tissue. Clinically, antazoline lowers the velocity of intraatrial conduction, prolongs the atrial refraction period and may improve atrioventricular conduction allowing fast ventricular response to supraventricular arrhythmias. The half-life of antazoline is considered to be about three hours with antiarrhythmic efficacy expiring after about one hour [7-9].

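### The planned Cox model rests on about two expected placebo conversions, so if treatment is a term there is a 13% to 19% chance of no finite hazard ratio

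*Protocol article*

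**What the plan says.** The Statistical analysis section of the protocol article plans Kaplan-Meier curves of return to sinus rhythm by treatment group and a log-rank test. It then adds: "Multivariate analysis will be carried out using Cox proportional hazards regression modeling". It does not say which terms enter the model or how it is to be estimated. Categorical variables are compared by continuity-corrected chi-square, or by Fisher's exact test when expected counts are small.

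The Sample size section supplies the event rates. For control, "Assumption of 5% efficacy of placebo was derived from studies over vernakalant". For active treatment, "Assumption of 50% efficacy in AF conversion is conservative". The conclusion is that "we need 80 patients, 40 in each group, to show the superiority of antazoline over placebo".

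Three further passages bear on the shape of the effect over time. The Background gives onset within minutes of administration and describes "antiarrhythmic efficacy expiring after about one hour". The Study group section gives boluses "every five minutes up to a cumulative dose of 250 mg or conversion of AF to SR". The Interventions section adds 1.5 hours of observation after the last dose.

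Time to conversion is a secondary end point, and the Objectives section calls secondary end points exploratory for lack of power.

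**The concern.** A Cox model estimates the treatment effect by comparing who converts with who is still at risk at each conversion. If nobody in one arm converts, the partial likelihood keeps rising as the hazard ratio grows. It has no finite maximum, and the Wald interval and p-value from such a fit mean nothing. With one or two conversions in that arm, the estimate exists but is very imprecise, and each added covariate makes it less stable.

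The design expects to be close to this situation. The concern is therefore not that the article omits modelling detail. It names a method that sits badly with the event count the same article plans for. At stake is the only adjusted analysis that the article names.

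There is a lesser question of proportionality. A drug that acts within minutes and wears off after about an hour is unlikely to multiply the conversion rate by the same factor throughout a longer observation window.

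**Working it through.** **Inputs.** Placebo 5%, antazoline 50%, 40 per arm, two-sided alpha 0.01, power 90%, drop-out 20% (Sample size). Five boluses of 50 mg at five-minute intervals, so 20 minutes from first to last (Study group). Observation of 90 minutes after the last dose (Interventions).

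**The plan's own figure.** Use the two-proportion formula with pooled proportion 0.275:

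- n = [2.576 × √(2 × 0.275 × 0.725) + 1.282 × √(0.05 × 0.95 + 0.50 × 0.50)]² / 0.45² = 26.7.
- With continuity correction: (26.7/4) × [1 + √(1 + 4/(26.7 × 0.45))]² = 31.0, so 31 per arm.
- With drop-out: 31/0.80 = 38.75, so 39 per arm and 78 in total, against 80 stated.

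The stated size is reproduced to within two patients, so the planning rates can be taken at face value.

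**Expected events.**

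- Placebo: 40 × 0.05 = 2.0. With 20% lost, 32 remain and 32 × 0.05 = 1.6.
- Both arms: 40 × 0.55 = 22. With 32 per arm, 17.6.

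**Chance of very few placebo conversions (binomial).**

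| True placebo rate | Patients | None | At most one |
|---|---|---|---|
| 5% | 40 | 0.95^40 = 12.9% | 39.9% |
| 5% | 32 | 0.95^32 = 19.4% | 52.0% |
| 2% | 40 | 44.6% | 81.0% |
| 3% | 40 | 29.6% | 66.2% |
| 10% | 40 | 1.5% | 8.0% |

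The 5% rows use the protocol's rate. The other rows are assumptions that show sensitivity.

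**Precision when the estimate is finite.** Under proportional hazards the planning rates imply a hazard ratio of ln(0.50)/ln(0.95) = 13.5. The standard error of its logarithm is about √(1/d1 + 1/d0), where d1 and d0 are the conversions in each arm.

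- 20 v 2: √(1/20 + 1/2) = 0.74, and exp(1.96 × 0.74) = 4.3. The interval around 13.5 is about 3.2 to 58.
- 20 v 1: √(1/20 + 1) = 1.02, a factor of about 7.5 either way.

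A simulation of 600 trials per scenario, with treatment as the only term and 40 per arm, gave a median ratio of upper to lower 95% limit of about 18 where the estimate was finite. This agrees with 4.3² = 18.5.

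**Proportionality.** From the first bolus, observation lasts 90 minutes after a single bolus and 20 + 90 = 110 minutes after five. Assume a constant placebo hazard over 110 minutes and a drug effect that stops at 60 minutes. The cumulative hazards are −ln 0.95 = 0.0513 and −ln 0.50 = 0.6931, so:

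- Before 60 minutes: [0.6931 − 0.0513 × 50/110] / [0.0513 × 60/110] = 0.670/0.0280, about 24.
- After 60 minutes: 1.

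If the effect stops at 80 minutes, the early ratio is about 18. In the simulation the median fitted hazard ratio was 13.0 both with the effect stopping at 60 minutes and with constant hazards. Non-proportionality therefore changes what the number means, while sparse placebo events dominate its uncertainty.

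**Contrast with the binary comparison.** At 20 v 2 the expected number of conversions per arm under the null is 22 × 40/80 = 11, and at 20 v 0 it is 10. The planned test works in both cases, and Fisher's exact test is available if counts are smaller.

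**The case against.** The strongest reply is that the article gives the Cox model a single sentence. It does not say that treatment is a term, lists no covariates and specifies no estimation or interval method. Such details commonly sit in a full protocol or analysis plan, and a Firth-penalised model is still Cox regression. This largely stands. The missing details are not themselves a fault, and the 13% to 19% figure is conditional on treatment being in the model. That is the natural reading, because the sentence follows a by-treatment time-to-event comparison. What survives is the mismatch between the named method and the planned number of placebo events.

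Stronger readings are tempting, and the documents do not support them:

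- *The hazard ratio will be uninterpretable.* It is finite in about 81% to 87% of trials at the planning rate. The 20 v 2 interval of 3.2 to 58 is wide but excludes 1, and the estimate can be read as an average over the window.
- *The protocol's pharmacology contradicts proportional hazards.* No shape is given for the placebo hazard, so a constant ratio is implausible, not refuted. The figure of 24 falling to 1 rests on an assumed constant placebo hazard.
- *Time to conversion loses its analysis.* The Kaplan-Meier curves and log-rank test remain usable with no placebo conversions. The Cox model is an addition to them.

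The 90 to 110 minute window also assumes timing from the first bolus, whereas the section's wording of the Kaplan-Meier time axis can be read as running from the onset of AF. The zero-event problem arises on either axis.

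**Conclusion.** The point holds as a minor one. On the protocol's own figures the named multivariate analysis has about two placebo events to work with. There is a 12.9% chance (19.4% with 32 evaluable per arm) that maximum likelihood yields no finite treatment hazard ratio, and the interval is wide when it does. This assumes that treatment is a term and that the true placebo rate is near 5%. The chance rises to 44.6% at 2% and falls to 1.5% at 10%, both with 40 per arm. Doubtful proportionality is secondary: it makes the estimate a window average without invalidating it. The primary conclusion does not depend on this model, and the end point it serves is declared exploratory.

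**What to change.** Specify the Cox model as Firth-penalised, with profile penalised-likelihood limits, timed from the first bolus, with treatment and at most one baseline covariate named in advance. Two terms is about what 22 expected events allow under a rule of thumb of ten events per term (an assumption: 22/10 = 2.2). The penalised model still assumes proportional hazards, so its hazard ratio should be described as an average over the window.

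Beside the Kaplan-Meier curves and log-rank test, report the between-arm difference in the proportion converted by fixed times, for example 30, 60 and 90 minutes from the first bolus. Ninety minutes is the latest time that a patient given only one bolus reaches under the stated observation rule, so 110 minutes would not serve. Use a Newcombe score-type interval, because a standard Greenwood variance is zero in an arm without events.

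For 20/40 v 0/40, the Wilson limits are 35.2% to 64.8% and 0% to 8.8%. The Newcombe limits for the 50% difference are:

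- Lower: 0.50 − √(0.148² + 0.088²) = 33%.
- Upper: 0.50 + 0.148 = 65%.

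This summary needs no proportionality and stays finite with zero placebo events.

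The cost is analysis wording only, with no change to sample size or conduct. The article reports that recruitment is under way, so the wording should be fixed before outcomes by arm are examined. The downside is that penalised hazard ratios are slightly shrunken and less familiar to readers.

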**Methods/design:**

A randomized, double blind, placebo-controlled, superiority clinical trial was designed to assess clinical efficacy of antazoline in rapid conversion of AF to sinus rhythm. Eligible patients will present AF lasting less than 43 hours, will be in stable cardio-pulmonary condition and will have no prior history of advanced heart failure or significant valvular disease. Long-term antiarrhythmic therapy is not considered an exclusion criterion. Subjects who fulfill selection criteria will be randomly assigned to receive intravenously either antazoline or placebo in divided doses and observed for 1.5 hours after conversion to sinus rhythm or after the last i.v. bolus. Primary end point will be the conversion of AF to sinus rhythm confirmed in an electrocardiogram (ECG) during the observation period. Secondary end points will be comprised of time to conversion and return of AF during the observation period. Special consideration will be given to the observation of any adverse events. A sample size of 80 patients was calculated based on the following assumptions: two-tailed test, a type I error of 0.01, a power of 90%, efficacy of placebo 5%, efficacy of antazoline 50% and 20% drop-out rate to fulfill the criteria of intention-to-treat analysis. Due to the presumed lack of statistical power, the secondary end points and safety endpoints will be considered exploratory.

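### The trial is sized at a two-sided type I error of 0.01, but every hypothesis is to be tested at 0.05, so the primary endpoint has two success thresholds

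*Protocol article*

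**What the plan says.** Three places in the protocol article give a type I error.

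- **Abstract, Methods/design:** the 80 patients rest on "two-tailed test, a type I error of 0.01, a power of 90%, efficacy of placebo 5%, efficacy of antazoline 50% and 20% drop-out rate".
- **Statistical methods, Sample size:** "Using a two-tailed test, a type I error of 0.01, a power of 90% and a 20% drop-out rate", leading to 40 patients per group.
- **Statistical methods, Statistical analysis, last sentence:** "All hypotheses will be two-tailed with a 0.05 type I error".

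The last sentence makes no exception for the primary endpoint. The Abstract and the Objectives section call the secondary and safety endpoints exploratory, but neither says that 0.05 is meant only for them. Nowhere does the article say that 0.01 was a deliberately strict value for sizing alone.

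**The concern.** A confirmatory trial with one primary endpoint needs one significance level for it. Here a primary p-value between 0.01 and 0.05 is a success under the analysis section and a failure at the level on which the trial was designed. With both values on file, the threshold could be settled after the result is known. The Blinding section adds weight to this, because the statistician is unblinded to assignment.

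The same sentence also attaches a 0.05 error rate to secondary and safety comparisons that are elsewhere exploratory, so it does not separate the confirmatory test from the rest.

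**Working it through.** **Inputs.** All come from the Sample size section: placebo conversion p₁ = 0.05 ("Assumption of 5% efficacy of placebo was derived from studies over vernakalant"), antazoline conversion p₂ = 0.50 ("Assumption of 50% efficacy in AF conversion is conservative"), two-sided test, power 90%, drop-out 20%, 40 per group. The test comes from the Statistical analysis section: chi-square with continuity correction, or Fisher's exact test if an expected count is below 5.

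**Step 1. Reproduce the stated 80 at 0.01.** With p̄ = (0.05 + 0.50)/2 = 0.275 and d = 0.45:

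n = [z₁₋α/₂ √(2p̄(1−p̄)) + z₀.₉ √(p₁(1−p₁) + p₂(1−p₂))]² / d²

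- √(2 × 0.275 × 0.725) = 0.6315 and √(0.0475 + 0.25) = 0.5454
- n = (2.576 × 0.6315 + 1.282 × 0.5454)² / 0.2025 = (1.6266 + 0.6990)² / 0.2025 = 26.7
- Continuity correction: n′ = (n/4)[1 + √(1 + 4/(nd))]² = 31.0
- Drop-out: 31/0.8 = 38.75, so 39 per arm, 78 in total

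This agrees with the stated 80 to within two patients. Without the correction the result is 27 per arm, or 34 after drop-out (68 in total).

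**Step 2. The same calculation at 0.05.** n = (1.2377 + 0.6990)² / 0.2025 = 18.5; corrected n′ = 22.7, so 23; 23/0.8 = 28.75, so 29 per arm, 58 in total. Without the correction the total is 48. Neither is near 80, so the design was built on 0.01.

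**Step 3. Where the verdict changes.** I applied the planned test to 2×2 tables with 40 per arm and 2 of 40 placebo conversions, the expected number at 5%.

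| Antazoline conversions | p | At 0.05 | At 0.01 |
|---|---|---|---|
| 9/40 | 0.051 | fail | fail |
| 10/40 | 0.028 | success | fail |
| 11/40 | 0.015 | success | fail |
| 12/40 | 0.008 | success | success |

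The gap is there for every placebo count from 0 to 4. For 0, 1, 2, 3 and 4 placebo conversions, the minimum on antazoline is 6, 8, 10, 11 and 13 at 0.05, and 8, 10, 12, 14 and 15 at 0.01.

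**Step 4. How often a result would fall in the gap.** Exact enumeration, 40 per arm. The first row is the protocol's assumption; the other two are my illustrative assumptions of a weaker effect.

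| Placebo vs antazoline | Power at 0.01 | Power at 0.05 | Chance of disputed result |
|---|---|---|---|
| 5% vs 50% | 98.4% | 99.75% | 1.4% |
| 5% vs 30% | 57% | 78% | 22% |
| 5% vs 25% | 36% | 60% | 24% |

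With 32 per arm (40 less 20%) and 5% vs 50%, power is 94.1% at 0.01 and 98.8% at 0.05, and the chance of a disputed result is 4.7%.

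**Step 5. Actual error rate of the planned test.** The test is discrete and conservative, so its realised size lies below the nominal level. With 40 per arm and a common conversion rate of 5%, it is 0.02% when tested at 0.01 and 0.4% when tested at 0.05. At a common rate of 20% the figures are 0.4% and 2.2%.

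**The case against.** The best reply is that 0.01 is only a sizing assumption and that the analysis section alone states how hypotheses are tested. Sizing at a stricter level than the one tested is conservative and leaves the test valid at 0.05, a conventional level. On that reading there is one rule, and the only fault is that its relation to the sizing value was not declared. Further points on that side:

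- The planned test is conservative. At the protocol's own 5% placebo rate, testing at 0.05 keeps the true false-positive rate near 0.4%, so a move from 1% to 5% describes the nominal levels only.
- Under 5% versus 50% a disputed result is rare (1.4%), and the expected result of 20/40 against 2/40 has p of about 0.00002.
- The sample size is sufficient at either level.
- Running exploratory comparisons at 0.05 does not in itself contradict calling them exploratory.

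These points are correct as arithmetic, and they limit the practical size of the problem. The last one also stands: the wording on secondary endpoints is loose rather than contradictory. But the conservative-sizing reading appears nowhere in the article, which states both levels without linking them. Nor does the low chance of a disputed result give much comfort, because it depends on 50% being right. The Background section describes the earlier evidence as mainly uncontrolled single-arm studies, and at 25% to 30% conversion between a fifth and a quarter of trials would fall in the gap. A separate analysis plan could not remove the conflict either: it could agree with one statement and would then contradict the other.

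**Conclusion.** The concern holds. The primary endpoint has two significance levels in current text, 0.01 in the design and 0.05 in the analysis, a fivefold nominal difference. The stated 80 patients follow from 0.01 (78 recomputed) and not from 0.05 (58). The trial is not underpowered and the test is not invalid; what is undefined is whether a p-value between 0.01 and 0.05 counts as success. At 2/40 placebo conversions that covers 10 and 11 antazoline conversions out of 40. The boundaries assume 40 analysed patients per arm and the test named in the Statistical analysis section. The chance of a disputed result depends on the true conversion rates, from 1.4% at the planned rates to about 24% at 5% versus 25%. Because this is the decision rule for the only primary endpoint, it must be settled before outcome data are compared by arm.

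**What to change.** Replace the last sentence of the Statistical analysis section with: *The primary hypothesis is tested two-sided at 0.01. All secondary and safety comparisons are exploratory and are reported with nominal p-values and confidence intervals, without claims of significance.* This agrees with the Abstract, the Sample size section and the 80 patients.

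If the sponsor really intends 0.05 for the primary test, the conflict can also be resolved by saying so, and by declaring in the Abstract and the Sample size section that 0.01 was a conservative value used for sizing only. Whichever level is kept, the decision should be dated and made by people who have not seen outcomes by arm.

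The cost is one sentence while the trial is still recruiting, with no extra patients. Power at 0.01 stays above the stated 90% under the planning assumptions (94.1% with 32 per arm). The real price of 0.01 is lower power than at 0.05 if the effect is weaker than assumed, for example 57% against 78% at 5% versus 30% with 40 per arm.
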